### Follow up

MACEs of participants will be followed up at 6 months, 12 months, 18 months and 24 months by reviewing medical document or death certificate or by telephone visit or by clinic visit. Ba-PWV will be re-tested at 12 months and 24 months (Table 1). An adjudication committee will review all events and confirm final  diagnosis.

**Table 1 Tab1:** Follow up schedule

Schedule	Baseline (July–December 2020)	Follow up			
Follow up schedule		1st follow up (June 2021)	2nd follow up (December 2021)	3rd follow up (June 2022)	4th follow up (December 2022)
Informed consent form	√				
Confirmation of inclusion and exclusion criteria	√				
Questionnaire investigation	√				
Physical examination	√				
Laboratory examination	√				
Vascular health assessment					
Endothelial function	√				
Ba-PWV	√		√		√
CAVI	√		√		√
ABI	√		√		√
Carotid ultrasound	√				
MACEs		√	√	√	√
Reasons for withdrawal or loss of follow-up		√	√	√	√

Ba-PWV, brachial ankle artery pulse wave velocity; CAVI, cardio ankle vascular index; ABI, ankle brachial index; MACEs, major adverse cardiovascular events

### Sample size estimation

About 1500 subjects will be included in this study, and the sample size was determined as follows:

### Incidence of end point events

The endpoint events concerned in this study are MACEs, the most important of which are coronary heart disease, stroke and related death. In previous studies, the standardized annual incidence of coronary heart disease in people over 45 years old in Beijing was estimated to be 497/100,000 [17], and the standardized annual incidence of stroke in people over 40 years old in China was estimated to be 533/100,000 [18]. Regardless of the difference in age composition of the population, during the 3-year follow-up period of this study, the incidence of CV events was estimated to be about 30/1000 people, and a total of about 45 cases of CV events could be obtained.

### Sample size calculation

This study is a prospective cohort study, and the main exposure factor is BVHS. BVHS is an ordered classification variable, taking the median of BVHS as the  reference, we regard the higher BVHS as the exposure group and the lower as the control group. The sample size of the cohort study was calculated by using the sample size formula of the cohort study when the sample size of the exposure group was equal to that of the control group: $${\text{n}} = 2 \times \frac{{\left( {z_{\alpha } \sqrt {2\overline{pq} } + z_{1 - \beta } \sqrt {p_{0} q_{0} + p_{1} q_{1} } } \right)^{2} }}{{(p_{1} - p_{0} )^{2} }}$$, α indicates the significant level, set to 0.05; 1-β indicates the test efficacy, set to 0.9; p_0_ indicates the incidence of the control group; $$q_{0} = 1 - p_{0}$$; p_1_ indicates the incidence for the exposure group, $$q_{1} = 1 - p_{1}$$; $$\overline{p} = (p_{0} + p_{1} )/2$$, $$\overline{q} = (q_{0} + q_{1} )/2$$; The incidence of natural population events was taken as the estimation of the incidence of the control group, that is $$p_{0} = 0.03$$, and the risk ratio (RR) value of the exposure group was used to estimate the incidence of the exposure group. According to the previous research results of our group [10], the RR value was estimated to be 1.94, $$p_{1} = p_{0} *RR$$. Under the above parameters, the minimum sample size is 1471.

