### Statistical analysis methods

Measurement data are expressed as mean and standard deviation (SD); classification and grade data are expressed as rate and constituent ratio. Chi-square test is used for classification and grade data; t-test or analysis of variance is used for measurement data; Pearson correlation and Spearmen rank correlation (rank data) are used for correlation analysis. For MACEs incidence during follow-up, we will use multivariate Cox regression models to test the difference between BVHS groups, adjusting for possible imbalanced variables at the baseline. We will also test if the intervention effect is modified by age, gender, cardiovascular risk factors and number of medications. Discrimination was evaluated by the C statistic. Calibration was assessed using a calibration plot. A *P* < 0.05 (two-side) is statistically significant. Data inventory and management using SAS (version 3.5.1, Vienna, Austria); all statistical analysis is completed by SAS (except for the construction of multi-level model needs to be combined with professional software MLwiN2.10).

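### The study is sized on a median split of an ordinal grade with an equal-groups formula, but the rule does not place median-grade participants and does not assure 1:1 groups

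*Protocol article*

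**What the plan says.** The protocol article, under Sample size calculation, makes BVHS the main exposure and states that "BVHS is an ordered classification variable". It takes the median as the reference, and "we regard the higher BVHS as the exposure group and the lower as the control group". The number of participants comes from a two-proportion cohort formula for the case "when the sample size of the exposure group was equal to that of the control group".

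The inputs are a significance level of 0.05, power of 0.9, a control incidence p0 of 0.03 and a risk ratio of 1.94 from the group's earlier study. The stated minimum is 1,471, and about 1,500 were planned. The Results section reports 1,648 enrolled.

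The section on statistical analysis methods sets a two-sided 5% level and compares BVHS groups by Cox regression. It does not say that those groups are the median halves. The grading itself is in Fig. 2, which is not reproduced in the text at hand. The text gives neither the number of grades nor their distribution.

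**The concern.** The exposure definition and the formula stand in the same paragraph and do not fit each other. A median split gives equal halves on a continuous scale. On an ordered scale with few levels and about 1,500 people, the median will very probably be a grade held by many of them. Those people are neither above nor below the reference, so the stated rule leaves them without a group. Whichever side they join, the halves are equal only if the cumulative share happens to reach 50% at a grade boundary.

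Two things are at stake. The first is the validity of the required number and of the stated power, because both assume 1:1. The second is that the contrast on which the study is sized has an open cut. With about 45 events expected (Incidence of end point events), moving a whole grade across that cut could change any high-versus-low estimate. The cut should therefore be fixed before events are seen.

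**Working it through.** **Inputs.** p0 = 0.03; p1 = 0.03 × 1.94 = 0.0582; difference 0.0282, squared 0.00079524; z = 1.960 (two-sided 0.05, as in the analysis section) and 1.2816 (90% power).

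**The plan's own figure, at 1:1.** The mean of p0 and p1 is 0.0441, with complement 0.9559.
- First term: 1.960 × √(2 × 0.0441 × 0.9559) = 1.960 × 0.29036 = 0.5691.
- Second term: 1.2816 × √(0.0291 + 0.05481) = 1.2816 × 0.28968 = 0.3712.
- Total: n = 2 × (0.5691 + 0.3712)² / 0.00079524 ≈ 2,223.8, so 2,224.

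The stated 1,471 is not reproduced. The sample-size paragraph does not state the number of sides. A one-sided test gives 1,814 (907 per group), which also does not match. With equal groups, power at 1,471 is 75.0% two-sided or 83.9% one-sided.

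**Unequal groups.** Let f be the exposed share and p̄ = f·p1 + (1 − f)·p0. Then

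N = [1.960·√(p̄(1 − p̄)(1/f + 1/(1 − f))) + 1.2816·√(p1q1/f + p0q0/(1 − f))]² / (p1 − p0)²

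At f = 0.5 this is the plan's printed formula. At f = 0.3, p̄ = 0.03846 and the two terms are 0.8225 and 0.6069, so N = (1.4294)² / 0.00079524 ≈ 2,570. Power at a given N is obtained by solving the same expression for the second z value. The shares f are assumptions.

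| Exposed share | N for 90% power | Power at 1,500 | Power at 1,648 |
|---|---|---|---|
| 20% | 3,311 | 62.9% | 66.4% |
| 30% | 2,570 | 71.5% | 75.2% |
| 40% | 2,285 | 75.4% | 79.1% |
| 50% | 2,224 | 75.8% | 79.7% |
| 60% | 2,344 | 72.8% | 77.0% |
| 70% | 2,705 | 65.1% | 69.6% |
| 80% | 3,576 | 49.9% | 54.4% |

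Across all splits the smallest N is about 2,222, near 48% exposed. The highest power is about 76% at 1,500 and about 80% at 1,648.

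**Median grade left out.** If a share m of participants is dropped and the rest divide equally, power at 1,500 is 71.4% (m = 10%), 66.3% (20%), 60.5% (30%) and 54.0% (40%).

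**How far from 1:1 can a median cut go?** At most half the cohort lies strictly above the median and at most half strictly below. Adding the tied share m to one side or the other gives two possible exposed shares. They lie m apart, one on each side of 50%. The more balanced choice is therefore within m/2 of 50%, so reaching 30:70 needs m of at least 40% and reaching 20:80 at least 60%. The less balanced choice can be up to m away, so 20% and 30% could be enough.

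**The case against.** The strongest reply is that the median split is only a device for using a two-proportion formula. It appears in the sample-size section and nowhere else. The analysis is a Cox model across BVHS groups with a C statistic and a calibration plot, and a Cox model on the grades themselves fits that wording equally well. This stands. A reader might infer that the study's main analysis contrast is undefined for much of the cohort, but the article does not fix the median halves as that contrast.

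A second reply is that the grade distribution is not shown, so a near-equal split is possible. This also stands: one may say that equal groups are not assured, but not that they are certainly missed. A moderate imbalance is cheap. At 1,500, a 40:60 split costs 0.4 points (75.8 − 75.4) or 3.0 points (75.8 − 72.8), depending on which group is larger.

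A third reply is that the large shortfall belongs to another error. That is right. The fall from 90% to about 76% occurs at exactly 1:1 and must not be charged to imbalance.

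A reader might also infer that a cohort-specific cut cannot be compared with the earlier risk ratio of 1.94. That depends on how the earlier study formed its groups, which the article does not say, so the inference is not supported.

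The mismatch itself remains. The paragraph chose both an ordinal median rule and an equal-groups formula, without placing the tied grade or justifying 1:1. That is a stated choice, not a detail left to an analysis plan.

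**Conclusion.** The point holds as a defect in how the study is sized. The rule does not place participants on the median grade, and an ordered scale does not assure the equal groups that the formula requires.

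The size of the effect is uncertain because the grade shares are not in the article. Relative to 1:1 at N = 1,500, two-sided, the loss of power is about 0.4 to 3 points at 40:60, 4 to 11 points at 30:70 (75.8 − 71.5; 75.8 − 65.1) and 13 to 26 points at 20:80 (75.8 − 62.9; 75.8 − 49.9). The wider splits need a large tied grade or an unfavourable placement of it.

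Independently of the split, 90% power is not reached. The two-sided requirement is never below about 2,220, and power at the 1,648 enrolled is at most about 80%. These figures rest on the plan's own p0 and risk ratio, a normal approximation, and no loss to follow-up.

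**What to change.** Before any event data are reviewed, state which BVHS grades form the higher group and which the lower, including the median grade. Replace the equal-groups formula by its unequal-allocation form, using the baseline grade proportions of the 1,648 enrolled. The article's follow-up schedule places the vascular assessments at baseline, so these proportions should be obtainable from data collected there, although Table 2 does not report them. Restate the required number and the power from that calculation, and correct the 1,471 at the same time.

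The cost is one paragraph of wording and one recalculation. No further enrolment is asked for. The price is a less favourable stated power: at most about 80% instead of 90%.

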## Background

Vascular health indicators, including lumen stenosis and dysfunction, both reflect the long-term cumulative effects of traditional and unidentified cardiovascular (CV) risk factors before and after clinical vascular events, and can be regarded as an alternative end point indexes for target organ damage and risk prediction [1]. Several markers have been considered as the reflection of vascular health, among them endothelial function, arterial stiffness and carotid atherosclerosis are the most common indicators [1]. Endothelial dysfunction may represent the effect of traditional CV risk factors on vascular health [2]. Arterial stiffness is increasingly recognized as a surrogate end point for cardiovascular disease (CVD) and as a risk factor for clinical hypertension [3, 4]. Carotid ultrasound measurement of intima-media thickness (IMT) along with carotid plaque are emerging as the focus of carotid artery ultrasound imaging for CV risk prediction [5]. Currently, studies on assessing vascular health use only one or more of these indicators [6–8]. Beijing Vascular Health Stratification (BVHS) was put forward to assess vascular health including all stages of vascular disease progression, from endothelial function to arteriosclerosis to vascular stenosis [9]. BVHS is a risk prediction tool using subclinical vascular measures such as endothelial function, arterial stiffness, carotid atherosclerotic plaques and artery stenosis by non-invasive detections. Furthermore, traditional risk factors are not included in BVHS, but are used as adjusted confounding factors to analyze the independent predictive role of BVHS.

All the markers are graded as artery functional injury or structural disease or both. Our previous retrospective study found that the BVHS was a comprehensive risk assessment system and was independent of traditional CV risk factors [10]. However, the previous study did not develop a strict study design and follow-up plan. Therefore, this study was designed as a prospective cohort study to verify the previous research results and further explore the clinical value of BVHS for the prediction of major adverse cardiovascular events (MACEs).

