## Aim

BVHS Study is designed to answer two important clinical questions: (1) A preliminary study on the value of BVHS in predicting MACEs independently of traditional CVD risk factors; and (2) A preliminary comparative study on the predictive value of BVHS and other risk prediction system model of CVD commonly used at home and abroad, such as the China-PAR Project [11] and the Pooled Cohort Equations [12].

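### The stated 90% power at 1471 does not hold for the planned test: the printed formula gives about 2224, and nothing allows for the covariate adjustment that Aim 1 requires

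*Protocol article*

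**What the plan says.** In the protocol article, Sample size calculation compares participants above and below the median BVHS grade in two groups of equal size: "The sample size of the cohort study was calculated by using the sample size formula of the cohort study". The inputs are a significance level ("α indicates the significant level, set to 0.05"), a power ("1-β indicates the test efficacy, set to 0.9"), a control-group risk of 0.03 and a risk ratio of 1.94 from the group's previous study. On the control-group risk it says: "The incidence of natural population events was taken as the estimation of the incidence of the control group". The result is a minimum of 1471. The formula has no covariate term.

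The Aim section asks a different question, the "value of BVHS in predicting MACEs independently of traditional CVD risk factors". Statistical analysis methods gives the test: "we will use multivariate Cox regression models to test the difference between BVHS groups", with adjustment for baseline variables, and sets the level ("two-side) is statistically significant"). The Background makes the traditional risk factors the adjusters. It also says that the vascular indicators "both reflect the long-term cumulative effects of traditional and unidentified cardiovascular (CV) risk factors".

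Incidence of end point events expects about 45 events over 3 years. Results reports 1648 enrolled.

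**The concern.** The only power figure in the article belongs to a crude comparison, whereas Aim 1 is an adjusted effect. By the article's own rationale BVHS should be correlated with the adjusters. That inflates the variance of the BVHS log hazard ratio by about 1/(1 − R²), where R² is the share of variance in BVHS group explained by the covariates. The calculation in effect sets R² to zero. Separately, the stated size does not follow from the printed formula.

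What is at stake is the reading of a null result. The study is meant to verify the independence from traditional risk factors that the group's retrospective study reported. A non-significant adjusted hazard ratio set against a stated 90% power could be taken as evidence that BVHS adds nothing, when the power for that test may be well short of 90%.

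**Working it through.** **Inputs from the article.** p0 = 0.03; RR = 1.94, so p1 = 0.03 × 1.94 = 0.0582; mean risk = (0.03 + 0.0582)/2 = 0.0441; difference = 0.0282; equal groups; power 0.90; alpha 0.05, two-sided as in Statistical analysis methods. **Assumed here:** R² from 0.1 to 0.4, since the document gives no value.

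**1. The plan's own figure.** The printed formula is N = 2 × [z_α √(2·p̄·q̄) + z_(1−β) √(p0q0 + p1q1)]² / (p1 − p0)².

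- √(2 × 0.0441 × 0.9559) = 0.2904; √(0.03 × 0.97 + 0.0582 × 0.9418) = 0.2897.
- Two-sided: (1.960 × 0.2904 + 1.2816 × 0.2897)² / 0.0282² = 1111.9 per group, so N = 2224.
- One-sided (the formula writes z_α): 906.1 per group, so N is about 1812.

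Neither is 1471. Continuity correction, unpooled variance, arcsine, log-risk-ratio and events-based versions at 90% power do not give it either.

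**2. Crude power at the actual sizes.** Power = Φ{[√(N/2) × 0.0282 − 1.960 × 0.2904] / 0.2897}.

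| N | Two-sided crude power |
|---|---|
| 1471 | 75.0% |
| 1500 | 75.8% |
| 1648 | 79.7% |

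**3. Proportions against Cox.** For HR 1.94 and a 1:1 split, 90% power needs (1.960 + 1.2816)² / [0.25 × (ln 1.94)²] = 95.7, so 96 events. At a risk of 0.0441 that is N of about 2177, close to 2224. Moving to an unadjusted Cox test therefore costs almost nothing.

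**4. Adjustment alone.** Granting a true 90% before adjustment, power = Φ[(1.960 + 1.2816) √(1 − R²) − 1.960].

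| R² | 0 | 0.1 | 0.2 | 0.3 | 0.4 |
|---|---|---|---|---|---|
| Power | 90% | 87% | 83% | 77% | 71% |

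**5. Both together.** Power = Φ{√[D × 0.25 × (1 − R²)] × ln 1.94 − 1.960}, with ln 1.94 = 0.6627 and D the number of events.

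| Events D | Source | R² = 0 | 0.1 | 0.2 | 0.3 | 0.4 |
|---|---|---|---|---|---|---|
| 73 | 1648 × 0.0441 = 72.7 | 81% | 76% | 71% | 66% | 59% |
| 66 | 1500 × 0.0441 = 66.2 | 77% | 72% | 67% | 62% | 55% |
| 45 | Incidence of end point events | 60% | 56% | 51% | 46% | 41% |

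The 45 and 66 differ because the incidence section applies 3% to the whole cohort (1500 × 0.03 = 45), while the formula gives 3% to the control group only.

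**6. Events needed for 90% after adjustment.** 95.7/(1 − R²), rounded up: 107, 120, 137 and 160 for R² = 0.1, 0.2, 0.3 and 0.4.

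**The case against.** **Most of the shortfall is not due to adjustment.** This stands. At N = 1500 the fall from 90% to about 76% comes from the non-reproducing 1471. A reader might infer from the combined figures that adjustment makes power far lower than 90%. The document does not support that: adjustment on its own costs about 3 to 19 points (step 4), and where in that range it falls depends on an R² that is not reported. The Background supports some correlation with traditional factors, but it names unidentified factors too and so does not establish a strong correlation.

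**The risk ratio of 1.94 may already be adjusted.** The Background calls the previous BVHS finding independent of traditional factors, and the sample-size section does not say which kind of ratio this is. If it is adjusted, no shrinkage of the effect need be feared, but the variance inflation remains. The figures above keep the hazard ratio at 1.94 throughout and assume no shrinkage.

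**The event counts are uncertain.** This also stands, in both directions. The 3% adds coronary heart disease and stroke only, while the MACE definition also covers all-cause death, TIA, heart failure and peripheral intervention, so events may exceed 73. Against that, Follow up schedules MACE ascertainment only to 24 months, while the sizing uses 3 years.

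**R² cannot simply be read off today.** Agreed. The article has no closed list of adjusters and reports no BVHS distribution for the 1648. The baseline measurements are scheduled for every participant, but the list must be fixed and BVHS graded first.

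**The article does not claim 90% for the adjusted test, and it calls the work preliminary.** Both are true and soften the point. Still, it is the only power stated for the study, and it fails even for the crude comparison.

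**Conclusion.** The point holds, as two distinct faults. The firm one is arithmetic: under the printed formula and a two-sided 5% level, 1471 gives about 75% crude power, and the 1648 enrolled give about 80%. The second is a mismatch between the sizing model and the analysis. The planned adjusted Cox test loses a further amount that the calculation ignores; its existence follows from the article's own rationale, but its size is known only under an assumed R².

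Together, power for Aim 1 at the enrolled size is about 81% if BVHS were unrelated to the adjusters and 59% at R² = 0.4; at 45 events the range is 60% to 41%. This rests on HR 1.94 after adjustment, a 1:1 split, no dropout, and the plan's own risks or event count. A median cut of an ordered grade need not give equal groups, and an unequal split would lower these figures further. The correction affects how a null result is interpreted; it does not show the study to be uninformative or wrongly conducted.

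**What to change.** Withdraw the claim that 1471 gives 90% power. In its place:

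1. List the traditional risk factors to be adjusted for in the Aim 1 Cox model.
2. Once BVHS is graded, and before any outcome is examined, estimate from the baseline data p (the share above the BVHS cut) and R² (BVHS group regressed on the listed factors).
3. Report power for the adjusted hazard ratio in the 1648 enrolled as Φ{√[D × p(1 − p) × (1 − R²)] × ln HR − 1.960}. Say whether the 1.94 is a crude or an adjusted ratio.
4. Tabulate this over a range of R² and D, including the 45 events of the incidence section and the roughly 73 implied by the formula's risks, and say which event basis is meant.

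Enrolment does not change. The cost is one recalculation, a fixed covariate list and a revised paragraph, and the stated power will be less favourable.

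### The 3% whole-cohort incidence is used as the risk of the low-BVHS half, which contradicts the article's own 45 events; a consistent calculation gives about 59% power at N = 1500

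*Protocol article*

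**What the plan says.** The Incidence of end point events section of the protocol article adds an annual coronary heart disease rate of 497/100,000 to a stroke rate of 533/100,000. It concludes that over three years "the incidence of CV events was estimated to be about 30/1000 people" and that "a total of about 45 cases of CV events could be obtained". Both statements describe the whole planned cohort of 1500.

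The Sample size calculation section divides that cohort at the median BVHS: "we regard the higher BVHS as the exposure group and the lower as the control group". It uses a two-proportion formula for equal groups. On error rates it states "α indicates the significant level, set to 0.05" and "1-β indicates the test efficacy, set to 0.9"; the Statistical analysis methods section makes the test two-sided. For the control risk it states "The incidence of natural population events was taken as the estimation of the incidence of the control group", which sets p0 = 0.03. It takes RR = 1.94 from the group's earlier study, sets p1 = p0 × RR, and reports a minimum total of 1471.

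**The concern.** Using a general-population rate for the controls is sensible when the controls represent the general population. Here they are, by construction, the half of the cohort with the better vascular grade. If BVHS predicts events at all (RR above 1), their risk must lie below the cohort average and the upper half's risk above it. Giving the lower half the average risk and multiplying up from there raises the baseline risk, the absolute difference and the expected number of events together.

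This is the only sample-size justification given for the primary outcome. A reader who takes the stated 90% at face value would read a null result as good evidence against an RR of 1.94. At about 59% power, a true RR of that size would be missed about four times in ten instead of one in ten.

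**Working it through.** **Inputs from the article.** Overall 3-year incidence 0.03; about 45 events in 1500; RR 1.94; equal halves; two-sided α = 0.05 (z = 1.960); target power 0.90 (z = 1.282); stated minimum 1471; planned N 1500; enrolled N 1648 (Results section).

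**1. The stated figure.** With p0 = 0.03 and p1 = 0.03 × 1.94 = 0.0582, the mean is 0.0441 and the article's formula gives

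N = 2 × (1.960 × √(2 × 0.0441 × 0.9559) + 1.282 × √(0.03 × 0.97 + 0.0582 × 0.9418))² / 0.0282² = 2 × (0.5691 + 0.3712)² / 0.0282² ≈ 2,224.

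A one-sided test gives 1,814. Neither reproduces 1471, which matches a two-sided test only at about 75% power (1,470). On the article's own p0 and p1, two-sided power is 75.0% at 1471, 75.8% at 1500 and 79.7% at 1648. That is a separate error, noted here so that its effect is not charged to p0.

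**2. The contradiction.** Events implied by p0 and p1 in two halves of 750: 750 × 0.03 + 750 × 0.0582 = 22.5 + 43.65 = 66.15, an average incidence of 4.41%. The preceding section gives 1500 × 0.03 = 45. Both cannot hold when RR = 1.94.

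**3. Consistent risks.** Require the halves to average 3%: p0 × (1 + 1.94)/2 = 0.03, so p0 = 0.06/2.94 = 0.0204 and p1 = 1.94 × 0.0204 = 0.0396. Expected events: 750 × (0.0204 + 0.0396) = 45, as stated.

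**4. Power with consistent risks**, same formula, two-sided 5%:

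| Total N | Article's p0 = 0.03, p1 = 0.0582 | Consistent p0 = 0.0204, p1 = 0.0396 |
|---|---|---|
| 1471 | 75.0% | 57.8% |
| 1500 | 75.8% | 58.6% |
| 1648 | 79.7% | 62.7% |

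For 90% power the consistent risks need N = 2 × (0.4728 + 0.3087)² / 0.01918² ≈ 3,320; for 80%, about 2,482. Holding overall incidence at 3%, the RR detectable with 90% power is 2.81 at 1500 and 2.66 at 1648. A one-sided test at 1500 would still give only 70.3%.

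**5. Check by events (Schoenfeld).** Events needed for 90% power: 4 × (1.960 + 1.282)² / (ln 1.94)² = 95.7, so 96. With 45 events: √45 × 0.6627/2 − 1.960 = 0.263, so power is 60.4%. This agrees with step 4.

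**6. Adjustment (assumption, not from the article).** The planned Cox model adjusts for baseline variables. If these explain a share R² of the variation in BVHS, the effective events are 45 × (1 − R²). R² of 0.1, 0.2 and 0.3 leave 40.5, 36 and 31.5 events and power of about 56%, 51% and 46%. The conclusion does not depend on this step.

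**The case against.** The strongest reply is that a contradiction does not show which side is wrong. The 3% covers coronary heart disease and stroke only: (497 + 533)/100,000 × 3 = 3.09%. The End points section defines MACEs far more broadly, adding all-cause death, TIA, unstable angina admissions, heart failure events and revascularisation. If overall MACE incidence were 4.41%, p0 = 0.03 would be coherent and only the 45 would need correcting. With RR 1.94 and halves that average to the assumed overall incidence, two-sided power at 1500 would be:

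| Assumed overall incidence | Power at 1500 |
|---|---|
| 3% (the article's figure) | 59% |
| 4% | 72% |
| 4.4% | 76% |
| 5% | 81% |
| 6% | 88% |

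This has force as a reason to report a range. It does not rescue the calculation. The article gives no higher incidence and counts 45 events itself, and even the 4.4% that makes p0 coherent yields 76%, not 90%. There is also a pull the other way: the Follow up section schedules MACE checks only to 24 months. Two years at the quoted rates give 2.06%, about 31 events in 1500 and roughly 43% power.

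Three lesser points. The full distance from 90% to 59% is not due to p0, since the 1471 error already brings power to about 76% at 1500. An ordered grade may not split exactly in half, but the article assumes equal groups, and under any split the lower group's risk must be below the average when RR exceeds 1. Finally, enrolment is complete and the aims are described as preliminary. That limits the remedy to the text but leaves the stated power wrong.

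**Conclusion.** The concern holds. The article applies the whole-cohort incidence to the lower-risk half of that cohort, and the resulting 66 events contradict the 45 it expects. On its own overall incidence and RR, power is about 59% at 1500 and 63% at the 1648 enrolled, against a claimed 90%. The p0 error alone accounts for a fall from about 76% to 59% at 1500, and from about 80% to 63% at 1648; the rest of the gap comes from the 1471 figure. Correcting that figure alone would still leave power overstated.

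These values assume a two-sided 5% test, an equal median split, RR 1.94, 3% overall incidence over three years and no loss to follow-up. A higher MACE incidence would improve the figure, but at N = 1500 it would have to exceed 6% to reach 90%.

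**What to change.** Make the two sample-size sections agree. With the present 3%, set p0 = 2 × 0.03/(1 + RR) = 0.0204 and p1 = 0.0396. Then restate the power as about 59% at 1500 and 63% at 1648 for RR 1.94, or give the RR detectable with 90% power (2.81 and 2.66 respectively). If the authors believe the broader MACE definition raises incidence, they should state and source that figure, change the 45 events to match, and show power over a range of incidences. Express the result in expected events, since the planned analysis is a Cox model.

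No additional enrolment is proposed. The results can be presented as preliminary, as the Aim section already does. The cost is a correction to the text and a less favourable power statement; no endpoint, model or procedure changes.

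### The stated minimum of 1471 does not follow from the plan's own formula and inputs, which require 2,224 (two-sided); at 1471 the power is about 75%, not 90%

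*Protocol article*

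**What the plan says.** The Sample size estimation section sets the study size: "About 1500 subjects will be included in this study, and the sample size was determined as follows". The Sample size calculation section then splits the cohort at the median BVHS grade into a higher (exposed) and a lower (control) half. It prints a formula for comparing two incidences in equal groups, with a leading factor of 2 so that n is the total.

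Every input is given there:
- significance level: "α indicates the significant level, set to 0.05"
- power: "1-β indicates the test efficacy, set to 0.9"
- control-group incidence: p0 = 0.03, taken from the general population over three years
- effect: "the RR value was estimated to be 1.94", with p1 = p0 × RR

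The stated result is "Under the above parameters, the minimum sample size is 1471". The Statistical analysis methods section adds the sidedness of the test: "A *P* < 0.05 (two-side) is statistically significant". The sample size sections mention no dropout allowance, continuity correction or other adjustment.

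**The concern.** Formula, inputs and answer all stand in one paragraph, so the answer can be checked directly, and it fails the check by a wide margin. The figure matters because it is the only justification offered for enrolling about 1500 people. A reader who sees a 90% power target and a cohort slightly above the stated minimum will assume a 10% chance of missing a true risk ratio of 1.94. If the real chance on those inputs is about one in four, a null or borderline association between BVHS and MACEs would be given more weight as evidence of no effect than the design supports.

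**Working it through.** **Inputs** (Sample size calculation, except the sidedness, which is from Statistical analysis methods)
- p0 = 0.03; p1 = 0.03 × 1.94 = 0.0582; p1 − p0 = 0.0282
- p̄ = (0.03 + 0.0582)/2 = 0.0441; q̄ = 0.9559
- z for 90% power = 1.2816
- z for alpha 0.05 = 1.960 two-sided (1.645 if read as one-sided)

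**Formula, as printed**

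n = 2 × [z_α·√(2p̄q̄) + z_(1−β)·√(p0q0 + p1q1)]² / (p1 − p0)²

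**Components**
- √(2p̄q̄) = √(2 × 0.0441 × 0.9559) = 0.29036
- √(p0q0 + p1q1) = √(0.0291 + 0.05481) = 0.28968
- (p1 − p0)² = 0.00079524

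**Attempt to reproduce 1471**
- Two-sided: 2 × (1.960 × 0.29036 + 1.2816 × 0.28968)² / 0.00079524 = 2,223.8, i.e. 1,112 per group and **2,224** in total.
- One-sided: the same with 1.645 gives 1,812.1, i.e. **1,813**.
- Shortfall against the two-sided figure: (2,224 − 1471)/2,224 = 34%.

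**Other readings tried, all at 90% power (total N, two-sided / one-sided)**

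| Variant | Two-sided | One-sided |
|---|---|---|
| Overline read as the mean of pq (unpooled variance) | 2,217 | 1,807 |
| Continuity correction | 2,364 | 1,952 |
| Arcsine | 2,171 | 1,770 |
| 1.94 read as an odds ratio | 2,456 | 2,001 |
| 1.94 read as a hazard ratio | 2,338 | 1,906 |
| Unrounded incidence, p0 = 0.0309 | 2,156 | 1,757 |
| Schoenfeld events (96 / 79) | 2,177 | 1,791 |
| Freedman events (103 / 84) | 2,336 | 1,905 |

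The per-group n alone is 1,112 or 907. Rounding of the risk ratio does not help: RR from 1.935 to 1.945 gives 2,244 down to 2,204 two-sided. None of these comes within 3% of 1471.

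**What 1471 does correspond to.** At two-sided power 0.75 the formula gives 735 per group, 1,470 in total. To return 1471 at two-sided 90% power would need RR of about 2.20, or p0 of about 0.044.

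**Power on the stated inputs.** Solving the formula for power with N/2 per group:

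z_(1−β) = [0.0282·√(N/2) − z_α × 0.29036] / 0.28968

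| N | z_(1−β), two-sided | Power, two-sided | Power, one-sided | RR detectable at 90%, two-sided |
|---|---|---|---|---|
| 1471 | 0.676 | 75.0% | 83.9% | 2.20 |
| 1500 | 0.701 | 75.8% | 84.5% | 2.19 |
| 1648 | 0.830 | 79.7% | 87.4% | 2.12 |

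The 1648 is the enrolment reported in the Results section.

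**The case against.** The arithmetic error cannot be defended, but its framing can be contested.

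- **Sidedness.** The sample size paragraph writes z_α, and the two-sided statement comes from another section. Read literally, the requirement is 1,813 and power at 1471 is 83.9%. This stands as a qualification, so the figures must be labelled two-sided. It does not rescue 1471, and the analysis section makes two-sided the better reading.
- **Not the study's actual power.** The percentages describe an unadjusted comparison of equal halves with no losses. The planned analysis is a multivariable Cox model, and an ordered grade need not split into equal halves at its median. This is fair: the figures are conditional on the plan's inputs. But the plan chose this formula, and the survival-based event counts in the table do not support 1471 either.
- **Enrolment exceeded the plan.** At 1648, two-sided power is about 80%, so the shortfall is smaller than at 1471. It is still short of 90%.
- **A preliminary study.** The Aim section calls both questions preliminary, and the comparison with other risk models is not sized by this calculation. Even so, the article states a power target and a minimum, and readers will rely on them.
- **Unknown cause.** Another risk ratio, incidence or power may have been used and misreported. This stands, and the correction should allow for it.

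**Conclusion.** The stated minimum is wrong as written. The printed formula and inputs require 2,224 participants at two-sided 5%, or 1,813 if one-sided. The claimed 90% power is not reached at 1471, 1500 or 1648 on either reading. Two-sided, the type II error on the plan's inputs is about 24% at 1500 and 20% at 1648, instead of 10%.

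These figures assume p0 = 0.03, RR 1.94, equal groups and no losses, and they are probably favourable to the plan. The inputs imply 1500 × 0.0441 ≈ 66 events, whereas the Incidence of end point events section expects about 45. If 3% is the incidence in the whole cohort, then p0 = 0.06/2.94 = 0.0204 and p1 = 0.0396. The same formula then needs about 3,319, and power at 1500 falls to about 59%. The conclusion here does not depend on that further point.

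**What to change.** In the Sample size calculation section:

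1. Replace 1471 with 2,224 in total (1,112 per group) for two-sided alpha 0.05 and 90% power. If 1471 came from a different risk ratio, incidence or power, print those inputs and justify them instead.
2. Write the first z-value as z(1−α/2), so that it agrees with the two-sided level in Statistical analysis methods.
3. State what the actual size offers on the stated inputs: two-sided power of about 76% at 1500 and 80% at 1648, or a risk ratio detectable with 90% power of 2.19 and 2.12. Say that these assume equal groups and no losses, and recompute them if the control-group incidence is revised.

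The cost is a correction to the text. Enrolment, design and analysis stay as they are; the stated power becomes less favourable.
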